### Interim analyses {21b}

Interim analyses are planned for baseline data collection. Epidemiological studies will be reported and, if appropriate, a comparison with data from another region will be explored. The study will automatically end with the last data collection in the last class after 6 months. Access to these interim results and the final decision on the termination of the study will be at the discretion of the study management (MK, AB, CS).

### Methods for additional analyses (e.g. subgroup analyses) {20b}

We plan to split all of the participant data into subgroups for comparisons between males and females, different school types, age categories (younger vs. older determined by school grade), and healthy vs. clinically relevant. Depending on the variables, different methods will be used (*t*-test, Wilcoxon test, chi-squared), but we prefer multilevel modelling to explore associations between intervention effects and student characteristics.

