One extremely important conclusion that can be drawn from the ongoing pandemic situation is that children and young people are suffering [6–8] due, among other factors, to adverse home conditions, family stress, or mental illness. Therefore, it is essential to provide rapid assistance and to develop and evaluate effective, efficient prevention programmes that are easy to access and implement [6]. As child and adolescent mental health is hugely multifaceted [7], we limit ourselves here to one risk factor of which we are all aware, and with which students have struggled a great deal over the last 2 years: stress [1, 2]. A very broad definition of stress goes back to Hans Selye, a twentieth-century physician, biochemist, and hormone researcher, who said “Stress is the nonspecific response of the body to any demand” [9]. There are many different definitions of stress depending on the context. In the behavioural sciences, stress describes the perception of a threat, which is reacted to with anxiety, emotional tension, and discomfort. Neuroendocrinological stress can be described as a reaction of the body, more precisely the sympathetic nervous system, to release ACTH and adrenal glucocorticoids in response to a stimulus [10]. In the psychological context, it is assumed that the induction of negative affective states (e.g. feelings of anxiety and depression) influences the pathogenesis of physical illnesses [11]. Chronic stress is likely to result in long-term or lasting changes in emotional, physiological, and behavioural responses, which in turn affect susceptibility to and progression of disease, including stressful events such as trauma [12]. The endocrine response triggered by stress is composed of two endocrine response systems that are particularly responsive to psychological stress: the hypothalamic-pituitary-adrenal (HPA) axis and the sympathetic-adrenal medulla (SAM) system [13, 14]. Cortisol as the primary effector regulates a wide range of physiological processes. The repeated and prolonged activation of the HPA and SAM systems can severely impair physiology and is therefore at increased risk for physical and psychiatric disorders [11]. Symptoms associated with stress include loss of appetite, headache, stomach pain, difficulty concentrating, sleep disorders [15], and a decrease in QoL [16]. Stress is perceived differently from person to person, has a cumulative effect, and is seen as one of the strongest predictors of mental illness [15, 17]. A survey of around 230,000 6–18-year-olds conducted by the Kaufmännische Krankenkasse in 2017 [18] revealed a significant increase in mental disorders among children and adolescents with stress being identified as the major issue. Another prospective cohort study reported depression or neurotic and somatoform disorders to be the main disorders comorbid to stress [19]. This finding is supported by a body of evidence conducted in other studies [20–22]. The increased stress in young people pertains not only to school and academic achievement, but also to further factors such as stress with parents (regarding both school and home life), overstimulation by media, bullying in social networks, or general fears, which all contribute to a higher stress perception. School and school-related stress is certainly a major concern, even in elementary school: Young children are vulnerable to stress and show stress symptoms, and it has been identified that girls are more susceptible to stress and are coping differently compared to boys [20, 23]. Stress levels among children and adolescents appear to be higher in more academic school types than in vocational schools [24], and rise during adolescence [25]. With respect to school, and specifically stress caused in school, it is necessary to address and prevent anxiety (separation anxiety, fear of school, social anxiety, and test anxiety) together with the students themselves [26]. Crucially, moreover, stress leads to neurocognitive alterations [27].

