#### Secondary objectives

In addition to the primary outcome, the evaluation of *LessStress* will include the following secondary outcomes: emotion regulation, self-compassion, sleep quality, depression index, anxiety index, self-injurious behaviour, eating disorder symptoms, and health-related quality of life. To investigate adolescents’ resources, we will assess protective and resilience factors (see Table 1 for further details).

**Table 1 Tab1:** Overview of the questionnaires being used

**Instrument**	**Content**	**Length**
**PSS-10:** *Perceived Stress Scale* (primary outcome measure)	Primary objective Developed by Cohen, Kamarck, and Mermelstein, translated and validated by Klein, Brähler et al., 2016 [47]. Investigates the degree to which life was unpredictable, uncontrollable, and overwhelming within the last month. Very good internal consistency (*a* = .84). Positive correlation with depression and anxiety, negative one with quality of life.	10 items
**DERS-SF***: Difficulties in Emotion Regulation Scale Short Form*	Measures emotion (dys-)regulation multidimensional. According to the model by Gratz and Roemer [48], the subscales “non-acceptance”, “problems with target oriented behaviour”, “impulsive conduct problems”, “lack of emotional awareness”, “limited access to emotion regulation strategies”, and “lack of emotional clarity”.	16 items
**SCS:** *Self-Compassion Scale*	The Self-Compassion Scale was developed by Neff in 2003 with 26 items. The shortened version showed satisfactory to good psychometric properties so far [49].	12 items
**WHO-5***: WHO Fragebogen zum Wohlbefinden*	The facets of psychological well-being like mood, interest, energy, and drive within the last 2 weeks are assessed. Used worldwide, non-invasive questions, translated in 30 languages, the first version was published in 1998. Very good internal consistency with *α* = .85. German version by Allgaier [50].	5 items
**PHQ-4***: Gesundheitsfragebogen für Patienten – Depressionsmodul*	The PHQ-4 is a valid screening instrument for symptoms of depression and anxiety symptoms (Cronbach α >0.80) [51]. Responses are scored as 0 (“not at all”), 1 (“several days”), 2 (“more than half the days”), or 3 (“nearly every day”). PHQ–4 scores go from normal (0 –2) to mild (3–5) to moderate (6–8) to severe (9 –12). Symptoms within the last 2 weeks are being interrogated.	4 items

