### Eligibility criteria {10}

#### Inclusion and exclusion criteria

Participants must be aged between 12 and 18 years and be in the 6th to 12th grade. We chose this age group for two reasons: (1) The onset of adolescence brings about a clear increase in social, cognitive, and emotional challenges and expectations. Furthermore, neurological and cognitive change processes are underway [60]. Taken together, this can correspondingly increase self-perceived stress. (2) Epidemiological data show that the end of childhood, the beginning of adolescence, and adolescence itself represent the period with the highest risk of onset of mental disorders [28, 61].

Only one exclusion criterion will be applied: lack of informed consent from the adolescents or their parents/guardians. Moreover, we will assess the presence of a psychiatric illness with accompanying psychotherapy in order to exclude these students from data analysis.

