#### Secondary outcome

Furthermore, we assume that adolescents, who show a lack of emotion regulation skills measured with the short form of the *Difficulties in Emotion Regulation Scale* (DERS-SF) [48], will show higher levels of stress, lower QoL, and more mental health problems. The DERS-SF yields a sum score out of 18 items ranging from 0 = *no difficulties at all* to 90 = *extreme lack of regulation strategies*.We assume a correlation between self-perceived stress and self-compassion insofar as the more stress students have, the less self-compassion they show. Therefore, we will measure self-compassion with the German short form of the *Self-Compassion Scale* (SCS-SF) [49].We assume that a lower subjective well-being (WHO-5) [68] will be associated with higher stress levels among adolescents.

The same patterns are expected for psychopathological measurements such as depressive and anxiety symptoms (PHQ-4) [51], eating disorder symptoms (SEED) [54], and poor sleep quality [53, 69]. In order to verify these hypotheses, we will look at the symptom level itself and will also try to create a “psychopathology-score” (PP score) for each participant. This score will be determined by grouping: For every questionnaire, a scale will be drawn up with three different ratings (normal, abnormal, and pathological) by splitting at the 25% and 75% confidence intervals, with normal = 0 points, abnormal = 1 point, and pathological = 2 points. This way an individual score can be calculated for each participant representing his or her psychopathological level of health/illness. Furthermore, we assume the lower the HrQoL, the higher will be the PP score.

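### The additional analyses examine age as younger versus older, although school grade has seven ordered levels; a graded interaction would use more of the information at almost no cost

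*Protocol article*

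**What the plan says.** Under Methods for additional analyses {20b}, the protocol article states: "We plan to split all of the participant data into subgroups for comparisons between males and females". The list goes on to school types and then to "age categories (younger vs. older determined by school grade), and healthy vs. clinically relevant". No grade is named as the boundary between younger and older. Neither the measure nor the threshold behind the clinical grouping is given.

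On method, the section says "Depending on the variables, different methods will be used", naming the t-test, the Wilcoxon test and chi-squared, and then adds "but we prefer multilevel modelling to explore associations between intervention effects and student characteristics". It does not say whether the characteristics enter those models as groups or on their full scale.

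The range of grade comes from the eligibility section: "Participants must be aged between 12 and 18 years and be in the 6th to 12th grade". That gives seven ordered levels.

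**The concern.** The stated purpose in {20b} is to learn whether the programme effect differs between kinds of students. For a universal programme, this bears on which grades it should be offered to. A two-group version of grade treats a 6th-grader and an 8th-grader as alike, and may treat an 8th-grader and a 9th-grader as different. If the effect changes gradually, part of the signal is lost and the answer depends on where the cut falls. No cut is fixed, so that choice would be made later.

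This is separate from clustering and from the choice of test. A multilevel model fitted to a younger/older indicator would lose the same information.

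**Working it through.** **The plan's own figures.** The sample size section gives a design effect of 1 + (80 − 1) × 0.05 = 4.95. Then 306 × 4.95 = 1514.7, taken as 1515, and 1515 × 1.25 = 1893.75, taken as 1894. These figures serve the main effect only. The document gives no power or target effect for any subgroup or interaction analysis. I use 1515 as the plan's own number before the dropout allowance; whether 306 is the right starting value is a separate matter.

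**Assumptions not in the document.** Grades 6 to 12 are equally filled, the programme effect changes linearly with grade, and it does not otherwise vary between schools. The test is two-sided at 0.05. The sizes of the moderation are chosen for illustration.

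**Step 1: information kept by a grade split.** This is the squared correlation r² between grade and its two-group version: r² = (difference in group means)² × p(1 − p) / variance. Equally filled grades 6 to 12 have variance 4 (SD 2). The two group means differ by 3.5 grades at any cut.

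| Cut | p(1 − p) | r² |
|---|---|---|
| 6-8 vs 9-12, or 6-9 vs 10-12 | 12/49 | 12.25 × 0.2449 / 4 = 0.750 |
| 6-7 vs 8-12 | 10/49 | 12.25 × 0.2041 / 4 = 0.625 |
| 6 vs 7-12 | 6/49 | 12.25 × 0.1224 / 4 = 0.375 |

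These losses do not depend on how large the moderation is.

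**Step 2: power when schools enter several grades.** Grade then varies within schools, and the interaction is estimated largely within them: z = slope × SD(grade) × √N / 2 / √(1 − ICC). The mid-range split multiplies z by √0.75 = 0.866. Power = P(|Z| > 1.96).

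- Effect falling from 0.4 SD in grade 6 to 0 in grade 12 (mean 0.2, the planned d): slope × SD = 0.4/6 × 2 = 0.133. z = 0.133 × 38.92 / 2 / 0.975 = 2.66, power about 76%. Split: z = 2.31, power about 63%. Loss about 12 points.
- Range of 0.3 SD: z = 2.00, power about 51%. Split: z = 1.73, power about 41%. Loss about 11 points.

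**Step 3: power when each school enters one grade of 80.** Grade is then a school-level variable and the full design effect applies. For the 0.4 SD range, z = 0.133 × 38.92 / 2 / √4.95 = 1.17, power about 21%. Split: z = 1.01, power about 17%. Loss about 4 points.

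**Step 4: the clinical split, conditional.** If it is a cut on a symptom score, and that score is roughly normal, the information kept is φ(z)² / [p(1 − p)], with φ the normal density at the cut. A median split keeps 0.637 (36% lost). A top-quarter split keeps 0.539 (46% lost). Neither cut is stated in the document for this grouping.

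**The case against.** The strongest reply is that {20b} does not fix how characteristics enter the preferred multilevel model, that such coding often belongs in an analysis plan, and that these analyses are exploratory with no decision attached. Part of this stands: the text does not rule out graded terms, and the weight of the point is small. But the groups are stated, not left open, and the preference for multilevel modelling does not replace them. For the main analyses, {20a} turns to mixed ANOVA unless the ICC exceeds 0.1, while the planning value is 0.05. It is therefore not safe to assume that a graded multilevel term will be fitted.

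A second reply is that the sample size section itself plans clusters of 80 from one entire grade. That makes the 4-point case the one closest to the plan, with power low under either coding. This also stands. The recruitment section lets a school enter several grades, so the larger loss is possible but not established.

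Three stronger readings are tempting, and the documents do not support them:

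- A reader might take the background sentence "Stress levels among children and adolescents appear to be higher in more academic school types than in vocational schools [24], and rise during adolescence" as evidence that the programme effect is graded by age. It concerns the level of stress, not the shape of the effect.
- A reader might infer that the clinical split must cut a continuous score because only scores are collected. The measures section also has a yes/no entry question on self-harm. The PHQ-4 comes with its own bands ("scores go from normal (0 –2) to mild (3–5) to moderate (6–8) to severe (9 –12"), so an established threshold is possible. The quartile-type split in the secondary outcome section ("by splitting at the 25% and 75% confidence intervals") makes three ratings and is not linked to this grouping.
- A reader might combine Steps 1 and 4 into one general loss of 25-46%. That would be neither a lower nor an upper bound, since off-centre grade cuts lose 37.5% or 62.5%.

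**Conclusion.** The point holds for grade. The plan states a two-group split of a seven-level ordered measure, without a cut or a reason, where a graded term in the already preferred model would do better against a gradual change. Under equally filled grades and linear moderation, the split loses 25% of the information at best and up to 62.5% at an extreme cut. With a mid-range cut, the power loss is about 10 to 13 points for effect ranges of 0.3 to 0.4 SD if schools enter several grades, and about 4 points at the 0.4 SD range if each enters one grade of 80.

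For healthy versus clinically relevant, the point is conditional. A loss of 36% to 46% applies only if the grouping is a median or top-quarter cut on a roughly normal score. If it rests on a clinical status, the argument does not apply.

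The primary comparison is untouched. This is a worthwhile refinement of exploratory analyses and no more.

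**What to change.** In {20b}, state that the multilevel model for the PSS-10 will include an arm by school grade interaction, with grade 6 to 12 entered as a score. Name the measure that defines clinically relevant. Where it is a questionnaire score, add an arm by baseline score interaction on the full scale. Report the estimated programme effect at selected grades and scores, and keep the younger/older and healthy/clinically relevant groups as descriptive displays.

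The cost is a sentence or two of text, with no new data, students or procedures. The one downside is that a linear interaction is less sensitive than the split if the true change is a sharp step exactly at the cut. The descriptive displays would still show such a step.

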### Sample size {14}

To analyse cluster-randomised trials, specific constraints must be followed, as individuals within a cluster are assumed to be more similar compared to individuals from different clusters. In order to detect significant effects, the sample size of the trial must be adjusted. This so-called clustering effect (1 + (*m*-1)×*p* [*m* = average number of subjects per cluster; *p* = intraclass correlation coefficient (ICC)]) resulted in an estimated *N* = 1795. For *m*, we assumed an average of 80 within an entire grade as the average class size in Germany varies nationwide (21.2–30.4 students per class), and the ICC was estimated quite conservatively at approximately 0.05 [70] on the basis of the primary outcome. Hence, a clustering effect of 4.95 was determined. Assuming a small effect size (Cohens *d* = 0.2) in universal prevention based on previous studies [71], with a significance level alpha = 0.05 and a power = 0.9, g*power suggests a total of *N* = 306 [72]. Considering the clustering effect, we have to multiply this by 4.95, reaching an overall *N* = 1515. Assuming a dropout rate of 25% due to moving out of the area, sickness, or other reasons, we must add another 379, leading to the final *N* = 1894.

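### The subgroup section permits t-tests, Wilcoxon and chi-squared tests that ignore school clustering and only prefers multilevel models; for between-school contrasts the type I error would be about 38% at 80 students per school and 25% at 40

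*Protocol article*

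**What the plan says.** The section on additional analyses {20b} gives the aim as follows: "We plan to split all of the participant data into subgroups for comparisons between males and females, different school types, age categories", followed by healthy versus clinically relevant students. On method it states: "Depending on the variables, different methods will be used", and lists the t-test, the Wilcoxon test and the chi-squared test. The same sentence ends by preferring multilevel modelling for studying how the intervention effect relates to student characteristics. It does not say when the single-level tests apply and when the multilevel model does.

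Three other sections bear on this:

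- Trial design {8} and Sequence generation {16a}: allocation is by school, 1:1.
- Sample size {14}: "individuals within a cluster are assumed to be more similar compared to individuals from different clusters". On cluster size, "we assumed an average of 80 within an entire grade"; on correlation, "the ICC was estimated quite conservatively at approximately 0.05". The resulting design effect is 4.95.
- Statistical methods {20a}: the clustered structure has to be respected, but multilevel models are used only if the ICC exceeds 0.1; otherwise mixed ANOVAs are used.

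**The concern.** The three named tests, in their standard form, treat every student as an independent observation. That conflicts with the assumption on which the article sizes the trial. Where the groups compared consist of whole schools, the standard error is too small and chance findings appear too often.

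The preference for multilevel modelling does not close the gap. It is not binding, and the only stated rule for choosing a method is the type of variable. It also refers to characteristics of students, whereas school type is a characteristic of schools, where clustering matters most. Nor can the subgroup section rely on the main analysis for protection: at the planned ICC of 0.05 the rule in {20a} leads to a mixed ANOVA.

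What is at stake is the credibility of subgroup statements, for example that school types differ or that the programme works in one type of student. Four subgroup factors and a long list of outcomes give many openings for such statements.

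**Working it through.** **Inputs.** From Sample size {14}: ICC 0.05, m = 80, and testing "with a significance level alpha = 0.05 and a power = 0.9". Sidedness is not stated; two-sided is assumed.

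**Step 1: reproduce the plan's own figure.** DE = 1 + (m − 1) × ICC = 1 + 79 × 0.05 = 4.95, as stated.

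**Step 2: type I error of a test that ignores clustering.** When whole schools are compared, the true variance of the difference is DE times what the test assumes. A nominal two-sided 5% test therefore rejects with probability 2 × (1 − Φ(1.96 / √DE)), where m is now the number of subgroup members per school.

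| Members per school (ICC 0.05) | DE | 1.96/√DE | Type I error |
|---|---|---|---|
| 80 | 4.95 | 0.881 | 37.8% |
| 40 | 2.95 | 1.141 | 25.4% |
| 26 | 2.25 | 1.307 | 19.1% |
| 20 | 1.95 | 1.404 | 16.0% |
| 10 | 1.45 | 1.628 | 10.4% |

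The 80 is the plan's cluster size, and 40 is half of it, as for one sex. The values 10 to 26 are assumptions: the article gives no subgroup size per school. The 26 merely lies within its class-size range ("21.2–30.4 students per class").

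**Step 3: sensitivity to the ICC at m = 80.**

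- ICC 0.01: DE 1.79, error 14.3%.
- ICC 0.02: DE 2.58, error 22.2%.
- ICC 0.03: DE 3.37, error 28.6%.

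**Step 4: simulation by type of contrast.** This used 24 schools of 80 (1894 / 80 ≈ 24), ICC 0.05, a random school intercept only, no true effect, 4000 runs and unadjusted tests.

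| Contrast | Rejection rate |
|---|---|
| School type vs school type | 37.6% |
| IG vs WL within one school type | 36.7% |
| IG vs WL within one sex (about 40 per school) | 25.5% |
| Male vs female | 5.2% |
| Arm-by-sex interaction | 4.9% |

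The formula and the simulation agree for between-school contrasts. In the last two rows each school contributes to both sides, so the school effect largely cancels and the error stays near 5%.

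**Step 5: age category.** The article sets it by school grade and takes the planning cluster as a whole grade. Where a school enrols a single grade, younger versus older is a comparison between schools, and the 80-member figure applies. Where a school enrols several grades, it is partly a within-school contrast.

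**The case against.** The strongest reply is that the section does name multilevel modelling as preferred for the question of who benefits, that {20a} acknowledges the clustering, and that these analyses are exploratory. All of this is true. It limits the weight of the point, but does not remove the permission to use single-level tests or supply a rule for when they apply.

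A reader might infer two stronger things that the article does not support:

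- **That subgroup results in general carry an error rate of 19% to 38%.** Male versus female and arm-by-sex stay near 5%. The 19% end rests on 26 members per school, which the article does not specify for any subgroup. The planning ICC is itself described as conservative, and lower values give smaller inflation. Healthy versus clinically relevant can also vary among students of one school; no figure was computed for it.
- **That the trial will test IG against WL separately inside each subgroup and read a difference in significance as effect modification.** The text speaks of comparing subgroups with each other. Separate arm tests are possible under its wording, but they are not stated.

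The article's leaving the clinical cut-off undefined is detail that a fuller document may hold, and is not part of this point.

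**Conclusion.** The point holds in limited form. The subgroup section permits tests that contradict the article's own clustering assumption and gives no commitment to the method that would respect it.

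For between-school contrasts the inflation is material: about 38% at 80 members per school and 25% at 40, against a nominal 5%. The lower figures in the working, about 10% to 19% for an assumed 10 to 26 members and 14% to 29% for an ICC of 0.01 to 0.03 at 80 members, remain above nominal. Contrasts that lie mainly within schools are not materially affected.

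These figures assume two-sided testing, equal cluster sizes, a random intercept for school only, and an ICC of the analysed score equal to the planning value unless varied. The primary comparison does not depend on this section, so the change is advisable rather than critical.

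**What to change.** In {20b}, remove the t-test, Wilcoxon and chi-squared option and the stated preference, and replace them with a commitment:

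- Subgroup questions are analysed with models that include a random intercept for school, fitted on all students; logistic versions are used for binary outcomes.
- This applies whatever ICC is observed. The section should not simply refer to the primary model, because {20a} drops multilevel models at an ICC of 0.1 or below.
- Effect modification is tested by a group-by-factor interaction for each named factor and reported with its confidence interval.

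The change costs wording only. The price in the results is wider, less favourable confidence intervals.
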